**Self-monitoring prompts**						
	Prompt	Upon enrollment; allocation ratio 1:1	Chat	Daily except Sunday; randomly between 10 am and 6 pm	1.6; 2.2; 4.1	Daily proportion of participant days that step goals were achieved
	Control (no prompt)	Upon enrollment; allocation ratio 1:1	N/A^b^	N/A	N/A	Daily proportion of participant days that step goals were achieved
**Planning**						
	Action planning	Upon enrollment; allocation ratio 1:1:1	Chat	Sundays; randomly between 10 am and 6 pm	1.4	Weekly proportion of participant days that step goals were achieved
	Coping planning	Upon enrollment; allocation ratio 1:1:1	Chat	Sundays; randomly between 10 am and 6 pm	1.2	Weekly proportion of participant days that step goals were achieved
	Control (no planning)	Upon enrollment; allocation ratio 1:1:1	N/A	N/A	N/A	Weekly proportion of participant days that step goals were achieved
**Incentives**						
	Cash incentives	Upon enrollment; allocation ratio 1:1:1	Dashboard/chat	Daily	10.2	Overall proportion of participant days that step goals were achieved
	Charity incentives	Upon enrollment; allocation ratio 1:1:1	Dashboard/chat	Daily	10.3	Overall proportion of participant days that step goals were achieved
	Control (no incentives)	Upon enrollment; allocation ratio 1:1:	N/A	N/A	N/A	Overall proportion of participant days that step goals were achieved

^a^1.2=problem solving, 1.4=action planning, 1.6=discrepancy between current behavior and goal, 2.2=feedback on behavior, 4.1=instruction on how to perform a behavior, 10.2=material reward (behavior), and 10.3=nonspecific reward.

^b^N/A: not applicable

**Table 3 table3:** Summary of collected sensor data.

Sensor	Variable	Data type	Frequency^a^
GPS^b^	Location	3D Float	Every 10 min
Accelerometer	Physical activity	Categorical	Continuous
Time	Time	Integer	Continuous
Proximity	Proximity of the phone	Binary (near and far)	Continuous
Wi-Fi	Wi-Fi connection	Categorical/string	Every 10 min
Bluetooth	Bluetooth connection	Categorical/string	Every 10 min
Ambient light	Ambient light	Float	Continuous
Battery status	Battery status	Float (charged in percentage)	Continuous
Screen events	Screen on/off	Binary (on/off)	Continuous

^a^Estimated frequencies only. Actual frequencies may vary depending on device and operating system.

^b^GPS: global positioning system.

For financial and charity incentives, postintervention differences in intrinsic and extrinsic motivation, and differences in app engagement and nonusage attrition during the intervention period are evaluated as additional secondary outcomes. Dimensions of intrinsic and extrinsic motivation are measured using the Behavioral Regulation for Exercise Questionnaire-2 (BREQ-2) [46]. As the external regulation subscale in the BREQ-2 exclusively relates to external regulation by other people, it is substituted by the more generally worded external regulation subscale of the Situational Motivation Scale (SIMS) [47]. Subscales of both instruments have shown good reliability (Cronbach alpha=.73-.86, BREQ-2 [46] and Cronbach alpha=.86, SIMS external regulation subscale [47]). Validity has been confirmed by factor analysis (BREQ-2) [46] and correlational analysis (SIMS) [47]. We measure engagement with the Ally app using the number and length of app launch sessions per day. An app launch session is defined as any interaction of the participant with the Ally app, separated by 5 min between events. If a participant left the app open and did not take action for 5 min or more, then the next interaction with the app counts as a new session. We coded a participant as “non-usage attrition observed” when she/he stopped using the Ally app at least 7 days before the end of the study.

#### Other Outcomes

As a preliminary pre-post evaluation of the Ally app, self-reported health outcomes and targeted mediators of behavior change were assessed at baseline and at postintervention follow-up. In addition, we assessed participant’s perceptions of the Ally app, of intervention components, and of the chatbot in addition to predictors of technology acceptance at postintervention follow-up. An overview of all measured variables is available in Multimedia Appendix 1 ([49-57]).

#### Sensor Data

Drawing on previous literature on context-aware mobile notification management systems [58], we identified smartphone sensors that may aid with predicting the participants’ state of receptivity. Sensor data were obtained from participants during the intervention period. Table 3 provides a summary of these sensors, their collected data, and their sensing frequency. In line with previous studies, we operationalize state of receptivity by using the response rate (ie, whether a participant responds to a notification or not) and the response time (ie, time between notification and response) to notifications of the Ally app.

### Sample Size

We used a simulation-based approach to estimate the power of our study design and determine the necessary sample size. As interaction effects require a greater number of participants to be detected with adequate power [59], we focused the power analysis on the two-way interaction effect of the between-subject factor incentives and the within-subject factor planning. We systematically varied the probability of reaching the step goal p (SG) when no intervention is provided (0.30, 0.40, and 0.50). These values seem reasonable given the fact the probability of step goal achievement according to the goal setting algorithm is 0.40. We further varied the increase in probability because of incentive and planning main effects (0.05, 0.10, and 0.15) and the interaction effect (0.05, 0.10, and 0.15) for sample sizes ranging from n=20 to n*=* 400. These effect sizes were based on previous studies on the use of incentives to promote physical activity [38,39]. A total of 100 simulations were generated for each scenario. *P* values of interaction effects were obtained by fitting generalized estimating equations (GEEs) models to the simulated data, and power was calculated as the proportion of *P* values below the significance level of alpha=.05. Figure 2 displays simplified results of this simulation with constant main effects of .15 and different values for p (SG) and the interaction effect. The black horizontal line indicates the recommended level of power of 1-beta=.80.

Simulations indicate that a sample size of roughly 220 is sufficient to detect an interaction effect of .05 with a power of 1-beta=.80 and alpha=.05 for p (SG)=.50. Sample sizes to detect an interaction effect .05 considerably increase for smaller values of p (SG) and smaller main effects (not shown). We, therefore, considered a sample size of 220 to be most feasible, and accounting for dropout, we set the target sample size for our study to 300.

**Figure 2 figure2:**
[figure not shown]
Results of the simulation-based power analysis. p (SG): probability of reaching the step goal.

### Recruitment and Eligibility

We invited insurees via email to participate in our study. On the basis of a previous study in the same population and with a similar recruiting process [60], we expected a participation rate of approximately 3%. We initially sent the invitation email to 10,000 insurees. However, because initial participation was lower than expected, an additional 20,000 insurees were invited to meet the required sample size.

The invitation email contained brief information about the study, eligibility criteria, and emphasized the benefits of participation. No details about the different intervention conditions were disclosed to the insurees. By following a link in the invitation mail, interested insurees were forwarded to an online survey platform, where they were screened for eligibility. Eligibility criteria were as follows: (1) German-speaking, (2) aged 18 years or older, (3) enrolled in a complementary insurance program, (4) being free of any medical condition that prohibits increased levels of physical activity, (5) not actively using an activity tracker or a comparable smartphone app, and (6) not working night shifts.

As meeting the first 3 eligibility criteria could be determined from the insurance company’s database, only insurees meeting these criteria were invited to participate. Due to legal regulations in Switzerland, the Ally app could be offered to insurees with complementary health insurance plans only. Note, however, that in Switzerland, 75% of people are enrolled in complementary insurance plans [61]. We excluded insurees working night shifts because interventions were sent out on prespecified times during the day only. Eligible insurees could subsequently obtain detailed information about the goals and study procedures, provide consent to participate, and enroll in the study. After enrollment, participants completed the first online questionnaire and subsequently received a 6-digit code, together with instructions on how to download and install the Ally app. Participants had to enter the code once upon first opening the Ally app to connect survey data and app data and to ensure that only study participants were using the app.

### Statistical Analyses

All analyses were prespecified before enrolling participants into the study. After completion of the study but before starting data analyses, the statistical methods for analyzing the effects of intervention components were changed from hierarchical linear modeling to a GEE-based approach to avoid biased effect estimates [62].

#### Primary Analyses

To evaluate main effects and interactions of intervention components, we will use the centered and weighted GEE approach described in the study by Boruvka et al [62]. This approach guarantees unbiased effect estimates when treatment and moderator variables are time-varying. Statistical models will evaluate each main effect and interaction of intervention components of interest on the components appropriate proximal outcome. For all main effects and interactions that include comparisons of multiple conditions, the main comparisons of interest are between the respective intervention and control conditions.

Missing data on covariates and on the dependent variable will be imputed using multiple imputation, provided the missing at random assumption is justified. We will perform sensitivity analyses to assess the robustness of the results of the primary analyses. These analyses include a per-protocol analysis and an adjusted analysis in which effect estimates are adjusted for a linear trend of time, baseline step count, and covariates of physical activity. For all tests, we use 2-sided *P* values with alpha<.05 level of significance.

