### Randomization, Allocation Concealment, and Blinding

The MobileCoach version used in this study requires the time point of dissemination for all dialogues to be known a priori. Therefore, randomization had to be performed upon enrollment of participants for all intervention components. Each participant was randomized to 1 out of 3 incentive conditions using simple randomization and an allocation ratio of 1:1:1. In addition, participants were randomized to 1 out of 9 planning intervention sequences (S_1_-S_9_) that determine the order in which the participant received the AP intervention, the CP intervention, or CC intervention throughout the intervention period. We used blocked randomization with a block size of 9 to achieve balance between the sequences. The resulting intervention schedule (Table 1) is uniform and strongly balanced, which controls for time and carry-over effects [45]. To avoid interference of self-monitoring prompts and planning, self-monitoring prompts were not delivered on Sundays. Thus, subtracting 6 from 42 left 36 available days for delivering self-monitoring prompts. To prevent repetition of content, we created 18 different versions of self-monitoring prompts that we randomly allocated to the 36 days for each participant. Consequently, at each of the 36 days, half of participants received a self-monitoring prompt (on average), whereas the other half received no prompt. All randomizations were performed using random number sequences generated with the shuffle-array package in JavaScript.

The fully automated randomization process guarantees allocation concealment for everyone involved in the study. Variables in the dataset indicating intervention allocation are encrypted to blind members of the research team involved in data analysis. A researcher at the Swiss Federal Institute of Technology in Zurich who is not involved in data analyses holds the decryption key and is instructed to safely store the key until the analysis script has been finalized. Due to the setting of the study, it is not possible to blind participants to intervention assignments. To reduce the impact of performance and attrition bias, participants were not informed about the details of the intervention components before the study.

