### Measurements

#### Primary and Secondary Outcomes

As the intervention components (see Table 2) are randomized on different timescales, we need to define primary and secondary proximal outcomes that correspond to these timescales to correctly evaluate the intervention components. The proportion of overall participant days that step goals are achieved during the intervention period is the primary outcome to evaluate the different incentive conditions. Weekly and daily proportions of participant days that step goals are achieved during the intervention period are the primary outcomes of the planning and self-monitoring prompts, respectively. On the same timescales, differences in steps per day measured with the smartphone are investigated as a secondary outcome.

**Table 1 table1:** Intervention schedule of the planning intervention.

Sequence	Week 1	Week 2	Week 3	Week 4	Week 5	Week 6
S_1_	AP^a^	AP	CP^b^	CC^c^	CC	CP
S_2_	CP	CP	CC	AP	AP	CC
S_3_	CC	CC	AP	CP	CP	AP
S_4_	AP	CP	CP	AP	CC	CC
S_5_	CP	CC	CC	CP	AP	AP
S_6_	CC	AP	AP	CC	CP	CP
S_7_	AP	CC	CP	CP	CC	AP
S_8_	CP	AP	CC	CC	AP	CP
S_9_	CC	CP	AP	AP	CP	CC

^a^AP: action planning.

^b^CP: coping planning.

^c^CC: control condition (no planning).

**Table 2 table2:** Overview of intervention components of the *A* ssistant to *L* ift your *L* evel of activit*Y* (Ally) app.

Component and intervention options		Randomization	Mode of delivery	Time of delivery	Behavior change techniques [48]^a^	Proximal outcome

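### The unconditional claims of unbiased estimates and carry-over control do not fit a planning schedule in which weeks 1 and 2 fix weeks 3 to 6; they need conditions and a lag-2 check

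*Protocol article*

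**What the plan says.** Under Statistical Analyses, the protocol article reports that the method was "changed from hierarchical linear modeling to a GEE-based approach to avoid biased effect estimates". Primary Analyses then applies one estimator to all components ("we will use the centered and weighted GEE approach") and adds: "This approach guarantees unbiased effect estimates when treatment and moderator variables are time-varying". No condition on the assignment mechanism is attached.

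That mechanism is set out under Randomization, Allocation Concealment, and Blinding:
- Timing: "Therefore, randomization had to be performed upon enrollment of participants for all intervention components".
- Planning: "participants were randomized to 1 out of 9 planning intervention sequences". Table 1 lists the nine six-week sequences of action planning (AP), coping planning (CP) and no planning (CC). The schedule "is uniform and strongly balanced, which controls for time and carry-over effects".
- Prompts: "we created 18 different versions of self-monitoring prompts that we randomly allocated to the 36 days for each participant". Each participant therefore has exactly 18 prompt days out of 36.

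**The concern.** A centered and weighted GEE for time-varying treatments centers and weights by the probability of treatment at each decision point. Its general unbiasedness result, including for time-varying moderators, takes that probability given the participant's past and needs it to lie strictly between 0 and 1. This is general methodological knowledge; the article itself says only that the approach is centered and weighted.

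Here planning is not drawn afresh each week. One draw at enrollment selects a fixed sequence, and prompts have a fixed total. If own history determines the option, the guarantee is unavailable in that form, and what remains depends on how long planning effects last. At stake are the planning contrasts with control, the week-by-week planning effects (change over time is a stated objective), and planning moderators such as activity level, which the Planning section names. The incentive comparison, a single 1:1:1 randomization, is not affected.

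**Working it through.** **1. The stated design properties reproduce.** In Table 1 each option appears twice per sequence and three times per week. Each of the nine ordered week-to-week pairs occurs 5 times (9 × 5 = 45 transitions). In every week from 2 to 6 all nine pairs occur once. The schedule is uniform and balanced for first-order carry-over.

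**2. Planning probability given own planning history.** The nine sequences have nine different week 1–2 pairs.
- Weeks 1 and 2: 1/3 for each option.
- Weeks 3 to 6: 0 or 1. That is 4 of 6 decision points (67%).
- Given only the previous week's option, it is still 1/3 in every week.

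**3. Lag-2 structure.**

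| Weeks | Option two weeks earlier → current option |
|---|---|
| 3 and 5 | AP→CP, CP→CC, CC→AP |
| 4 and 6 | AP→CC, CP→AP, CC→CP |

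Of the 36 lag-2 transitions, each of the six unlike pairs occurs 6 times and no option recurs. Within a single week, the current option is a one-to-one function of the option two weeks earlier.

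**4. Bias with marginal 1/3 under an additive lag-2 effect λ common to AP and CP.**
- Weeks 3–6: of the 12 AP cells, 6 follow CP and 6 follow CC, so the mean carry-over is λ/2. All 12 CC cells follow AP or CP, so the mean is λ. AP − CC = λ/2 − λ = −λ/2.
- All six weeks: each option has 18 cells, and the 6 in weeks 1–2 carry nothing. AP − CC = 6λ/18 − 12λ/18 = −λ/3.
- CP − CC gives the same two results.
- By week: AP − CC is −λ in weeks 3 and 5 and 0 in weeks 4 and 6. CP − CC is 0 in weeks 3 and 5 and −λ in weeks 4 and 6.

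The documents give no lag-2 effect. For scale, assume λ = 0.05, the smallest planning main effect in the Sample Size section. The bias is then −0.0167 pooled, −0.025 over weeks 3–6, and −0.05 in single weeks, with an alternation that could be read as a change over time. An additive lag-1 effect gives zero bias, pooled and by week.

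**5. Can lag 2 be estimated?** With week effects and current, lag-1 and lag-2 options, the 54-row design matrix from Table 1 has rank 12 of 12. Under independent errors the variance factor for the current AP effect rises from 0.1111 to 0.1333, a ratio of 1.2. Within any one of weeks 3 to 6, an intercept plus current and lag-2 options has rank 3 of 5, so the two cannot be separated.

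**6. Prompts.** After k prompts, the probability on day t is (18 − k)/(37 − t). Exact enumeration gives 0 or 1 on an expected 1.89 of 36 days (5.3%), concentrated at the end: 10.4% on day 33, 22.9% on day 34, 48.6% on day 35 and 100% on day 36. It lies within 0.3–0.7 on 88.5% of days. The probability is 17/35 after a prompt day and 18/35 after a day without one. An assumed lag-1 effect of 0.05 therefore biases the contrast based on 1/2 by 0.05 × (17/35 − 18/35) = −0.0014.

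**The case against.** The defense is substantial. The marginal probabilities of 1/3 and 1/2 are known and never 0 or 1, so the analysis can be run. Main effects and the planning-by-incentive interaction that sized the trial condition on nothing shaped by earlier planning. Action planning concerns the coming week, and no two-week effect is documented. Uniform and strongly balanced is standard crossover language for first-order balance, which the schedule has. Moderation is labeled exploratory. Which probabilities enter the weights could be a detail left to an appendix that is not shown.

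Most of this stands, and it rules out three stronger readings that a reader might infer:
- That the planning analysis cannot be computed. This is true only of probabilities conditional on full planning history.
- That lag-2 carry-over is fully aliased. It is aliased within a single week, but the pooled model has full rank because the lag-2 mapping differs between weeks 3/5 and 4/6.
- That prompt probabilities are often 0 or 1. This applies to about 5% of decision points, and the main-effect bias is negligible.

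What does not stand is the defense of the wording. The article asserts a guarantee and carry-over control without conditions, and its own design supplies only conditional versions. A two-week route is also built in. Step goals use the past 9 days, so in a seven-day planning week the goals on the first two days draw directly on steps from the week before last, and goal attainment is the primary outcome. The size and sign of that route are unknown.

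**Conclusion.** The point holds in a limited form. The estimator is usable for planning with marginal 1/3, and is unbiased for the main effects and the planning-by-incentive interaction if carry-over is additive and lasts at most one week. Beyond that condition, each pooled contrast with control carries −1/3 of a common lag-2 effect (−1/2 over weeks 3–6). Week-specific planning effects in weeks 3–6 cannot be told apart from lag-2 carry-over. Moderators shaped by planning two or more weeks earlier, such as recent activity level, lose the claimed protection; baseline moderators and those that planning does not affect keep it. The illustrative −0.0167 rests on an assumed λ of 0.05 and is not evidence that such an effect exists. For prompts, only analyses with history-dependent moderators need attention. The documents do not support discarding the GEE: a crossover model with a re-randomization test would be a legitimate preference, not a necessary correction.

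**What to change.** Keep the GEE and make these changes before the analysis script is finalized and the allocation key released:

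1. State that planning is centered and weighted with marginal 1/3. Replace the guarantee with its condition: no planning carry-over beyond one week.
2. Limit the carry-over claim for Table 1 to first order.
3. Add the lag-2 planning option to the pooled model as a sensitivity analysis.
4. Do not interpret week-specific planning effects in weeks 3–6 as free of lag-2 carry-over.
5. For planning moderators that earlier planning could have shaped, use baseline versions or restrict the analysis to weeks 1–2.
6. For history-dependent prompt moderators, use (18 − k)/(37 − t) and drop decision points where it is 0 or 1. For the prompt main effect, 1/2 is adequate if stated.

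No new data are needed. The cost is about 20% more variance for the planning effect in the sensitivity analysis (under independent errors) and narrower moderation claims for planning in weeks 3–6.

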### The Assistant to Lift Your Level of Activity App

The Ally app focuses on measuring and increasing walking, a popular and safe activity [9,10] that is known to have positive health effects independent of other types of physical activity [11]. Steps per day as an objective measure of walking can be obtained from the majority of commercially available smartphones with acceptable accuracy [12]. The Ally smartphone app tracks participants’ daily step counts and provides interventions to help participants reach daily step goals. It contains a dashboard that displays basic information such as the participants’ current step count and the step goal of the current day as well as an activity overview of the past 7 days (Figure 1). Ally runs on the common operating systems Android and iPhone operating system (iOS). On Android smartphones, Ally obtains all physical activity–related information from GoogleFit, a health-tracking platform developed by Google. On iOS smartphones, the same information is obtained from the HealthKit, an application programming interface for health apps provided by Apple. To obtain smartphone sensor data, we used EmotionSense, a framework to support smartphone-based data collection originally developed for experimental social psychology research [13].

Step goals are personalized and calculated daily for each participant based on the participant’s activity over the past 9 days employing the moving-window percentile-rank algorithm described by Adams et al [14]. This adaptive goal-setting algorithm sets the daily step goal to the sixtieth percentile of the participant’s step count distribution of the past 9 days, meaning that the participant reaches her or his step goal 40% of the times when maintaining her or his recent activity level. Previous studies demonstrated that this adaptive goal setting outperforms static step goals [14,15]. To facilitate maintenance of behavior change, adaptive step goals are capped at 10,000 steps per day, which approximates the World Health Organization recommendations for physical activity [16,17].

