### Baseline Characteristics

Baseline and demographic characteristics of participants are presented in Table 4. Participants (mean age 41.73 years; 57.7% [158/274] female) were mostly Swiss (246/274, 89.8%) and walked on average 6336 (SD 2701) steps per day during the baseline period. The distribution of age and gender is comparable with those of other studies evaluating physical activity apps [66,67]. Self-reported physical activity and comparisons of self-reported health with the German 12-item Short Form norm sample indicate that on average, participants in our study may be healthier and more active than the general population.

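### For the between-subject incentive comparisons, baseline step count enters only a sensitivity analysis, which gives up precision that the planned adjusted model could supply cheaply

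*Protocol article*

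**What the plan says.** Under Primary Analyses the protocol article states of main effects and interactions that "we will use the centered and weighted GEE approach". It then adds "We will perform sensitivity analyses to assess the robustness of the results of the primary analyses", and one of these is "an adjusted analysis in which effect estimates are adjusted for a linear trend of time, baseline step count, and covariates of physical activity". The article does not use the word unadjusted. But if the model containing baseline steps is the robustness check, the primary model is by implication the one without them. Secondary Analyses applies the same modelling approach to steps per day.

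On allocation, the section on randomisation says: "Each participant was randomized to 1 out of 3 incentive conditions using simple randomization and an allocation ratio of 1:1:1". No stratification is stated. Planning is assigned in blocks of nine balanced within-person sequences, and prompts fall on 18 of 36 days within each participant.

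Study Design describes a 12-day baseline period without interventions. Baseline Characteristics reports that participants "walked on average 6336 (SD 2701) steps per day during the baseline period", and Table 4 shows the count missing for 76 of 274. The goal is the 60th percentile of a participant's own last nine days, and "adaptive step goals are capped at 10,000 steps per day".

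**The concern.** The incentive contrast compares different people, so it carries the full between-person variance, and simple randomisation does nothing to even out activity level across arms. The trial measured that activity level over 12 days beforehand. Leaving it out of the primary model gives up information that is already in hand.

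Precision is not plentiful. Enrolment was 274 against a target of 300, and step data exist for 227. The value of baseline steps should differ by outcome. It should be high for steps per day, because active people stay comparatively active. For goal attainment it is less obvious, because the goal moves with each person's own recent steps. There the cap is the main link: someone who regularly walks more than 10,000 steps faces a goal below their own 60th percentile and meets it more often.

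**Working it through.** The article gives no precision figure for the incentive contrasts, so there is none to reproduce. Its sample size of roughly 220 concerns the incentive-by-planning interaction. The link and factor coding are not stated, and closed-form power at 220 runs from 0.42 to above 0.99 depending on them. That figure can be neither confirmed nor called wrong, and nothing below depends on it.

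**1. Chance imbalance in baseline steps between two arms.** Inputs: SD 2701 (Baseline Characteristics); 274 enrolled and 227 with step data (Recruitment); three equal arms on average. Formula: SD of the difference = 2701 × √(2/n).
- n = 274/3 ≈ 91: 2701 × √(2/91.3) = 400 steps; 95% range ±783; probability of a difference above 500 ≈ .21.
- n = 227/3 ≈ 76: 2701 × √(2/76) = 438 steps; 95% range ±859; probability above 500 ≈ .25.

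This is about 0.15 to 0.16 of a baseline SD.

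**2. Steps per day.** The SE ratio after adjustment is √(1 − r²), where r is the correlation between baseline and intervention-period mean steps. The article does not give r; .6 to .7 is assumed.
- r = .6: √(1 − .36) = .80, SE 20% smaller.
- r = .7: √(1 − .49) = .71, SE 29% smaller.

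A simulation in which each person's true level stays constant gives a larger cut, about 36 to 75%. Because real activity drifts, the lower figures are the safer ones.

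**3. Goal attainment.** The goal rule was simulated over 12 baseline and 42 intervention days (60th percentile of the last nine days, cap 10,000), with baseline mean 6336 and SD 2701. Two inputs are not in the article and were varied: day-to-day coefficient of variation (CV) 0.3 to 0.6, and extra between-person SD in attainment, unrelated to baseline, of 0 to 0.15. R² is the share of variance in person-level attainment explained linearly by the baseline mean.

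| CV | extra SD | R² | SE ratio √(1 − R²) |
|---|---|---|---|
| 0.3 | 0 | .388 | .78 |
| 0.3 | 0.15 | .109 | .94 |
| 0.4 | 0 | .304 | .83 |
| 0.4 | 0.15 | .070 | .96 |
| 0.6 | 0 | .144 | .93 |
| 0.6 | 0.15 | .021 | .99 |

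The SE falls by about 1 to 22%. With the cap removed, R² is at most about .02, so nearly all the gain comes from the cap. Table 4 has 21 participants above 10,000 steps, or 21/198 = 10.6% of those with a baseline count.

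**4. What an imbalance does to the estimate.** In the same simulations, a 400-step imbalance moves the attainment difference by 0.3 to 0.9 percentage points, against an unadjusted SE of 0.9 to 2.6 points.

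**5. Prompts and planning.** For goal attainment, baseline steps explain 0.2 to 1.6% of day-level variance, so the SE falls by under 1% (√(1 − .016) = .992). Both components vary within person, and a covariate that is constant within a person has little left to explain.

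**The case against.** The strongest reply is that nothing here is wrong. An unadjusted comparison of randomised arms is valid; chance imbalance does not bias it, and its SE and P value already allow for it. That stands, and it limits the point to efficiency.

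A reader might infer that the plan leaves open which result counts if the two analyses differ. It does not: one is labelled primary and the others are robustness checks. A reader might also extend the point to all three components. Step 5 shows that it does not reach prompts and planning.

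That the primary model is unadjusted is inferred. The article says "Missing data on covariates and on the dependent variable will be imputed using multiple imputation" without tying those covariates to a model, and it refers the overview of analyses to Multimedia Appendix 2, which is not shown. The appendix might add detail, but the article itself places the baseline-adjusted model among the sensitivity analyses.

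Missing data are the most practical objection. Baseline counts are absent for 27.7%. Imputation is conditional on missing at random, and Strengths and Limitations attributes some missing step data to never answering the chatbot. This dilutes the gain and makes the primary result depend on how the gaps are handled. It argues for stating that handling, not for leaving the covariate out.

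Finally, the change would come after data collection and after an earlier change of method. It remains defensible while allocation variables are encrypted and analysis has not begun, which is the position the article describes.

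**Conclusion.** The point holds for the incentive contrasts on goal attainment and steps per day, as an avoidable loss of precision. It is not a bias, a wrong figure or an inconsistency.

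The case is stronger for steps per day, a secondary outcome: an SE about 20 to 29% smaller at an assumed correlation of .6 to .7. For goal attainment, the primary outcome, the gain is anywhere from about 1% to 22%. The documents cannot narrow that range, because they give neither the day-to-day variation nor the between-person spread in attainment; a single firm percentage would claim too much. All these figures assume complete baseline counts and a linear difference scale, so with 27.7% missing the real gains will be smaller.

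The incentive-by-planning interaction used for sample size rests largely on within-person differences, so little gain should be expected there.

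One condition deserves stating. Randomisation took place at enrolment, so baseline steps were recorded after allocation. Adjustment is sound provided the incentive arm was not revealed during the baseline period, which fits the article's account that no interventions ran then and that details were withheld beforehand.

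**What to change.** Before the allocation variables are decrypted, name the already planned adjusted model as primary for the incentive contrasts on goal attainment and on steps per day, and report the unadjusted model as the sensitivity analysis. The prompt and planning analyses can stay as they are. Use the adjusted model as planned, with its covariate list fixed in the script; a non-linear baseline term would be a new specification and is not needed for this change.

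State how the 76 missing baseline counts will be handled: through the planned multiple imputation or, if missing at random is judged unjustified, with a missing indicator. Record the change, its date and the fact that it preceded unblinding.

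The cost is small. Both models are already planned, and no new data are needed. The price is dependence on the missing-data handling and one more documented change after data collection.
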